## Abstract

**Introduction:**

Prevention of necrotising enterocolitis (NEC) is vital for improving neonatal outcomes. Feeding own mother’s milk helps prevent NEC. Rates of own mother’s milk feeding in the East Midlands are lower than the national average and the incidence of NEC is higher. The East Midlands Neonatal Operational Delivery Network (EMNODN) has created a care bundle to improve these in babies born at <32 weeks’ gestation, the group at the highest risk of NEC. The bundle was introduced in September 2022 and embedded by December 2022. We will evaluate its effectiveness and conduct a process evaluation to understand barriers and facilitators to implementation.

**Methods and analysis:**

We will conduct a retrospective cohort study (workstream 1) using data from the National Neonatal Research Database (NNRD). We will identify infants receiving any own mother’s milk on day 14 and at discharge, and cases of severe NEC. We will aggregate outcomes by birth month and use interrupted time series analysis to estimate an incidence rate ratio for changes after the care bundle was embedded, relative to pre-implementation. We will model data from all other NNRD units and assess whether there are any concurrent changes to exclude confounding due to other events.

We will apply the RE-AIM framework (workstream 2), supplemented by the Consolidated Framework for Implementation Research and Framework for Implementation Fidelity, to conduct a mixed methods evaluation in EMNODN units. We will triangulate data from several sources, including questionnaires and semistructured interviews with parents and healthcare professionals, and data from patient records.

**Ethics and dissemination:**

The study has approval from the South East Scotland Research Ethics Committee 01 and the Health Research Authority and Health and Care Research Wales (IRAS 323099). Results will be disseminated via scientific journals and conferences, to neonatal service commissioners and through public-facing infographics.

**Trial registration number:**

NCT05934123.

Strengths and limitations of this studyUse of data from the National Neonatal Research Database allows comparison of all infants admitted to neonatal units in the East Midlands with a control group of all infants admitted to units elsewhere in England and Wales.Interrupted time series analysis will allow any changes in own mother’s milk feeding and the incidence of necrotising enterocolitis (NEC) related to implementation of the care bundle to be identified over and above any underlying changing trends.The parallel mixed methods process evaluation will allow us to unpack the ‘how’ and ‘why’ underpinning the results of the interrupted time series analysis.Analysis of routine data will allow all eligible infants to participate without risk of under-recruitment from underserved groups. In the process evaluation, we will purposively seek to include parents from underserved groups who traditionally hesitate to participate in research.NEC is a rare occurrence and so statistical power to detect small changes in incidence related to implementation of the care bundle may be limited.

## Introduction

Necrotising enterocolitis (NEC) is a serious, life-threatening disease in preterm infants.^1^ An estimated 12% of infants born weighing <1500 g develop NEC and 30% of these die.^2^ Survivors have increased risk of adverse neurodevelopmental outcomes, including cerebral palsy and cognitive impairment.^3^ Encouraging and supporting own mother’s milk feeding prevents NEC and has several additional advantages, including improved long-term neurodevelopment and parent–infant bonding.^4^ Health economic analysis estimates that if all premature infants were to be fed own mother’s milk, the total lifetime cost saving to the National Health Service (NHS) would be £46.7 million (£30.1 million in the first year of life), and there would be 238 fewer deaths per year with a gain of £153.4 million in lifetime productivity.^5^

Neonatal critical care services in England are commissioned by NHS England and managed within 11 neonatal operational delivery networks, to ensure that babies and their families receive high-quality, equitable and accessible care. The East Midlands Neonatal Operational Delivery Network (EMNODN^6^) comprises 11 neonatal units across seven NHS trusts, covering an area of 15 627 km^2^, a total population of approximately 4.9 million^7^ and approximately 47 000 live births per year.^8^ In 2022, EMNODN units provided 50 443 days of care in total to infants born preterm, or unwell at term, who needed specialist neonatal care; 476 infants were cared for who were born before 32 weeks’ gestational age (GA) and survived at least 48 hours.^9^

The rate of NEC in the EMNODN has remained above the national average since 2017, when this measure was added to the National Neonatal Audit Programme (NNAP).^10^ Additionally, there are wide variations between the 11 units that comprise the EMNODN. Rates of any breastmilk feeding at discharge from EMNODN units have been consistently below the national average, again with wide local variations.

The EMNODN has created a NEC care bundle^11^ which was introduced to the 11 neonatal units in September 2022, with use fully embedded by December 2022. Care bundles are a group of evidence-based, simple-to-implement interventions related to a disease or care process that, when executed together, result in better outcomes than when implemented individually.^12^ The EMNODN NEC care bundle consists of recommendations and parent-facing information to promote own mother’s milk feeding and optimise nutritional care of preterm infants. Early start and continuation of feeding with own mother’s milk such that babies go home breast feeding is vital to ensure babies continue to receive own mother’s milk throughout neonatal care and remain at a reduced risk of NEC.

There is some evidence that quality improvement (QI) programmes using care bundles can improve rates of own mother’s milk feeding in neonatal units. In the East of England, introduction of a care bundle increased the prevalence of own mother’s milk feeding from 50% to 57%.^13^ However, no previous studies have explored the effect of complex, multicomponent interventions such as a care bundle on rates of NEC and other feeding practices, and there are no published process evaluations of intervention implementation.

### Objectives

Our study comprises two parallel, integrated workstreams with the following objectives:

Workstream 1: Estimate the effects of implementation of the NEC care bundle on rates of own mother’s milk feeding and incidence of NEC, comparing infants admitted to the 11 EMNODN neonatal units with admissions to all other units in England and Wales. We will also describe feeding practices before and after implementation of the care bundle and examine the infant, maternal and unit-level characteristics associated with own mother’s milk feeding and NEC.

Workstream 2: In a multicentre, mixed methods process evaluation in the 11 EMNODN neonatal units, evaluate how well the care bundle was implemented, understand barriers and facilitators to implementation and understand which components contributed most to effectiveness.

## Methods and analysis

### Design

Parallel, integrated workstreams:

Workstream 1: Retrospective cohort study using routinely collected clinical data, with interrupted time series (ITS) analysis.

Workstream 2: Multicentre, mixed methods process evaluation based on the RE-AIM framework,^14 15^ Consolidated Framework for Implementation Research (CFIR)^16^ and Framework for Implementation Fidelity (FIF).^17^

### Setting

Workstream 1: Neonatal units in England and Wales, comparing infants admitted to the 11 neonatal units in the EMNODN with infants admitted to all other units.

Workstream 2: The 11 neonatal units that comprise the EMNODN.

### Time period

1 January 2016 to 30 September 2023, with infants grouped by date of birth into three groups according to date of implementation of the care bundle: pre-implementation period—1 January 2016 to 31 August 2022; implementation period—1 September 2022 to 31 December 2022; evaluation period—1 January 2023 to 30 September 2023, followed up for 3 months (until 31 December 2023) to cover the full neonatal stay of the final participant.

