#### Primary outcomes

Receiving any own mother’s milk at discharge (exclusively or in combination with infant formula).Receiving any own mother’s milk on day 14 of life (exclusively or in combination with infant formula).Severe NEC requiring surgery or resulting in death.^26^

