We will aggregate outcomes by month of birth (or by 2-month period if necessary to improve statistical power, without detriment to interpretation of results) and plot time series graphs to show the number of cases of each outcome per month over the study period in the EMNODN units combined. We will use a quasi-Poisson generalised additive mixed model^28^ to estimate an incidence rate ratio (IRR) for changes in the incidence of the outcomes in EMNODN units during the evaluation phase, relative to the pre-implementation period. Data for the 4-month implementation phase will be plotted graphically but excluded from statistical modelling as this period is too short to be able to model changes in incidence compared with the pre-implementation period. We will similarly plot and model data for infants admitted to units in the control group, to assess whether there are any changes in the IRR to exclude confounding due to other events or interventions which occurred around the time that the care bundle was introduced.

We will incorporate several covariates into our models as follows:

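### Births in about June to August 2022 are coded unexposed even if the infant was discharged after the bundle began, which modestly dilutes the estimated effect on feeding at discharge

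*Protocol article*

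**What the plan says.** Under Time period, the article defines three periods "with infants grouped by date of birth into three groups according to date of implementation of the care bundle". The first is the "pre-implementation period—1 January 2016 to 31 August 2022"; births from September to December 2022 form the implementation period, and births from January to September 2023 the evaluation period. The same section has the last evaluation births "followed up for 3 months (until 31 December 2023) to cover the full neonatal stay of the final participant".

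On timing, the abstract states: "The bundle was introduced in September 2022 and embedded by December 2022".

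Under Data analysis strategy: workstream 1, "We will aggregate outcomes by month of birth" sets the time unit (2-month periods if needed). The step variable is 0 for all pre-implementation births and 1 for evaluation births. Only the four implementation months are left out of the model.

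The first primary outcome is "Receiving any own mother’s milk at discharge", and the first secondary outcome is exclusive own mother's milk at discharge. The Introduction makes clear that the bundle acts on the later stay as well as the start: "Early start and continuation of feeding with own mother’s milk such that babies go home breast feeding is vital".

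**The concern.** Exposure is fixed at birth, but the discharge outcomes are measured at the end of the stay. An infant born in August 2022 and discharged in October spent much of the stay in a unit that was introducing the bundle, yet counts as unexposed. The article allows 3 months of stay after the last evaluation birth but makes no matching allowance before 1 September 2022.

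The affected months sit immediately before the interruption, where they have most influence on the trend carried forward into 2023. If the bundle raises feeding at discharge, these months lift the end of the baseline and shrink the estimated change. The control series cannot reveal or correct this, because the early exposure occurs only in the East Midlands units.

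**Working it through.** **Inputs.** There are 80 baseline months (January 2016 to August 2022), so June to August 2022 are months 78–80. Months 81–84 are excluded and months 85–93 are the evaluation period. Baseline prevalence is 55% with about 23 infants per month (Sample size calculation). If 23 counts infants fed own mother's milk, admissions are 23/0.55 = 41.8 per month; the 2022 figure of 476 infants gives 476/12 = 39.7. The target is a 15-point rise, so the true IRR is 70/55 = 1.273 and its log is 0.241.

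**The plan's own figure.** The article states 80% power for +15 points and about 90% for +20. A step-only Poisson model at 41.8 per month, dispersion 1 and two-sided 5% gives 83.6% and 97.1%. The pair is not reproduced, but alpha, dispersion and autocorrelation are not given, so I do not call it an error. Nothing below depends on it.

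**Who overlaps.** On 1 September 2022, June births are 63–92 days old, July births 32–62 and August births 1–31. Assuming one common stay and even births:

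| Stay (assumed) | June | July | August | All three |
|---|---|---|---|---|
| 30 days | 0% | 0% | 97% | 33% |
| 45 days | 0% | 45% | 100% | 49% |
| 60 days | 0% | 94% | 100% | 65% |
| 90 days | 93% | 100% | 100% | 98% |

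**Leverage.** For a straight line through 80 months, month i has weight 1/80 + (x0 − 40.5)(i − 40.5)/42,660 in the projection to month x0, where 42,660 = (80³ − 80)/12. For January 2023 (x0 = 85), months 78–80 together carry 3/80 + 44.5 × (37.5 + 38.5 + 39.5)/42,660 = 0.0375 + 0.1205 = 15.8%. For May 2023 (x0 = 89) it is 16.9%. An equal share would be 3.75%.

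**Dilution.** I fitted the segmented log-linear model with an admissions offset, linear trend and step to expected counts in which June, July and August births carry a given share of the full effect. Variants added season (harmonics in place of the spline), a lockdown indicator (months assumed) and the slope change. The average effect is taken at the middle evaluation month. The shares are assumptions.

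| Share of effect, Jun/Jul/Aug | Average log effect lost | IRR (true 1.273) |
|---|---|---|
| 0/6/27% | about 2% | 1.27 |
| 10/25/40% | 4–5% | 1.26 |
| 20/50/80% | 9–11% | 1.24 |
| 100/100/100% (upper bound) | 19–22% | 1.21–1.22 |

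With both slope and season terms, the step coefficient alone loses about 6% at 20/50/80%; the larger figures are for the average effect.

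**Against the standard error.** At Poisson variance the SE of the average log effect is about 0.082–0.085. A 2% loss is 0.02 × 0.241 = 0.005, or 0.06 SE. A 10.5% loss is 0.025, or 0.3 SE. If the estimated dispersion were below 1, so that the SE was nearer 0.061, the latter becomes 0.025/0.061 = 0.4 SE.

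**After dropping months 78–80.** The fit returns 1.273. The SE rises from 0.082 to 0.085 (step only) or from about 0.085 to 0.089 (season and lockdown added), which is 4–5%. Step-only power for +15 points is about 84% with a clean baseline, 76% at 20/50/80% and 81% after dropping the months.

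**Other outcomes.** A birth on 18 August reaches 14 days of age on 1 September, so only births from about that date can be affected for day-14 feeding.

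**The case against.** The strongest case is that grouping by birth is a reasonable choice and the overlap is slight. The bundle starts around birth. Infants born before September missed antenatal counselling, oropharyngeal colostrum and early nutrition, so birth cohort separates infants with the whole bundle from those with part of it at most. It was embedded only by December, and September births are themselves set aside as transitional, so giving August births 80% of the full effect is hard to defend. The 3 months is an allowance to cover the whole stay, not a typical stay. A transition window already exists, and the bias runs towards no effect, so it cannot create a false claim of benefit.

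Most of this stands, and it is why the size is put at 2–10% and not at the upper end alone. It does not remove the point: the boundary and the 0/1 coding are fixed in this document, the outcome is measured after the boundary for some infants coded 0, and the bundle explicitly aims at continued feeding to discharge.

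A reader might infer that many infants from all three months were exposed. The article gives no length-of-stay distribution, and June births are involved only if stays exceed two months. A reader might also infer that the analysis plan lacks a sensitivity analysis on this. That plan is not shown and may contain one; the criticism is of the stated period rule.

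**Conclusion.** The point holds as a modest, one-directional weakness in the period rule for the two discharge outcomes. If the bundle improves feeding at discharge, the average log effect is understated by about 2–10%, with an upper bound of about 20% if all three months were fully exposed. That is about 0.1–0.4 SE in the plausible range. It rests on assumed lengths of stay and assumed early uptake, neither of which the article gives, and on a true change from 55% to 70%. If the bundle has no effect, there is no bias from this source.

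It would be tempting to extend the point to all three primary outcomes. The document does not support that: day-14 feeding is touched only for births from about 18 August. The article gives no timing for NEC onset, but the effect there is also likely small, and the study is powered only for about a two-thirds reduction in NEC.

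**What to change.** For any and exclusive own mother's milk at discharge, end the pre-implementation period at births on 31 May 2022 and exclude births from 1 June to 31 December 2022 from the model, keeping the month numbering 1 to 93. Alternatively, keep the current window as primary and pre-specify this exclusion as a sensitivity analysis. If 2-month periods starting in January 2016 are used, June falls in the same period as May (months 77–78), so state how that period is handled.

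The cost is three of 80 baseline months and an SE about 4–5% larger (about 0.085 to 0.089 at Poisson variance and 42 admissions per month). No new data are needed.

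For day-14 feeding and NEC, leave the primary window as it is. A sensitivity analysis without August 2022 births is optional.

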### Eligibility criteria

For workstream 1, we will include infants who: were born at <32 weeks’ GA; survived at least 48 hours from birth; and were admitted for neonatal care from 1 January 2016 to 30 September 2023 to a neonatal unit contributing data to the NNRD. In line with previous work,^18 19^ we will exclude infants with missing data on key characteristics (eg, sex, GA, final discharge destination) as well as infants admitted >12 hours after birth and those missing data for one or more episodes of care.

For workstream 2, we will include parents of infants who: are admitted to one of the 11 EMNODN neonatal units in a 6-month period after implementation of the care bundle; are born at <32 weeks’ GA; and survived at least 48 hours from birth. All eligible parents will be invited to respond to the questionnaires. For the interviews, parents will be purposively sampled to include: parents from different neonatal units; parents of extremely preterm infants (born at 22–27 weeks’ GA) and very preterm infants (born at 28–32 weeks’ GA); parents whose infants received own mother’s milk, mixed feeding or did not receive any own mothers’ milk; parents of infants who had suspected or confirmed NEC; and parents representing different maternal (eg, education) and environmental (including socioeconomic) factors.

We will recruit HCPs working in EMNODN neonatal units. All HCPs will be invited to respond to the questionnaires and some will be purposely sampled to include a range of individuals representing different job roles (unit leads, consultants, junior doctors, nurse practitioners, nurses, healthcare assistants and allied health professionals including dietitians, speech and language therapists) and hospital sites.

All questionnaire respondents and interview participants will provide written informed consent for their participation and use of the data provided, including deidentified direct quotations in study outputs.

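### Follow-up to 31 December 2023 does not cover the full neonatal stay of the most preterm infants born late in the evaluation period, and the exclusion rule would then remove them

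*Protocol article*

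**What the plan says.** Under Time period, the protocol article gives the "pre-implementation period—1 January 2016 to 31 August 2022", a four-month implementation period, and the "evaluation period—1 January 2023 to 30 September 2023". Infants are "followed up for 3 months (until 31 December 2023) to cover the full neonatal stay of the final participant".

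Under Eligibility criteria, workstream 1 takes infants who "were born at <32 weeks’ GA; survived at least 48 hours from birth". No lower gestation limit is given. For the parent interviews, the same section names "parents of extremely preterm infants (born at 22–27 weeks’ GA" as a sampling group. It also states that "we will exclude infants with missing data on key characteristics (eg, sex, GA, final discharge destination" among the examples, together with "those missing data for one or more episodes of care".

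The first primary outcome is "Receiving any own mother’s milk at discharge". The other two, milk on day 14 and severe NEC, do not depend on discharge in the same way. The model includes a change-in-trend term that runs from 1 to 9 over the evaluation months.

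**The concern.** The article offers the cut date as sufficient for every stay to be complete, but gives no length-of-stay figure to support it. For the least mature infants, 92 days ends before or around term.

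An infant still in hospital at the cut has no discharge feeding status and no final discharge destination. Applied as written, the exclusion rule takes that infant out of the whole workstream 1 cohort, although day-14 feeding is already recorded and NEC status has been observed up to the cut. The infants lost are the most immature, whom one would expect to have the highest NEC risk. They are lost only at the end of the series, at trend values 8 and 9, where single months have most influence on the fitted slope. At stake is an avoidable bias in a primary outcome, in a study meant to inform national roll-out.

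**Working it through.** **Step 1: the plan's own figure.** 30 September to 31 December 2023 is 31 + 30 + 31 = 92 days, or 92 / 7 = 13.1 weeks. The stated three months is correct as a length. The question is whether it covers the stay.

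**Step 2: maturity at the cut.** PMA at the cut = gestation at birth + 13.1 weeks. For births on 30 September 2023:

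| Gestation at birth (weeks) | 22 | 23 | 24 | 25 | 26 | 27 |
|---|---|---|---|---|---|---|
| PMA at the cut (weeks) | 35.1 | 36.1 | 37.1 | 38.1 | 39.1 | 40.1 |

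**Step 3: follow-up needed.** Days needed = (PMA at discharge − gestation at birth) × 7. Uncovered final birth days = days needed − 92, or zero if negative. PMA at discharge is not in the document, so three assumed values are shown, as days needed / uncovered days:

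| Gestation (weeks) | Discharge at 36 weeks | Discharge at 40 weeks | Discharge at 44 weeks |
|---|---|---|---|
| 22 | 98 / 6 | 126 / 34 | 154 / 62 |
| 23 | 91 / 0 | 119 / 27 | 147 / 55 |
| 24 | 84 / 0 | 112 / 20 | 140 / 48 |
| 25 | 77 / 0 | 105 / 13 | 133 / 41 |
| 26 | 70 / 0 | 98 / 6 | 126 / 34 |
| 27 | 63 / 0 | 91 / 0 | 119 / 27 |

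The coverage statement holds for all gestations only if even a 22-week infant goes home by about 35 weeks. In the longest case shown, 154 days after 30 September 2023 is 2 March 2024; counted back from the present cut, cover for such infants ends with births on 30 July 2023.

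**Step 4: which periods are affected.** The last pre-implementation birth (31 August 2022) has 487 days to the cut, and the last implementation birth (31 December 2022) has 365. Truncation is in practice confined to the evaluation period, and within it mainly to August and September births.

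**Step 5: likely size.** The Introduction gives 476 eligible infants in the network in 2022, so 476 / 12 × 9 = 357 over nine months. The sample size section gives NEC at about 7%. The remaining inputs are assumptions:

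- 25% to 33% of infants born below 28 weeks;
- mean discharge PMA of 36 to 40 weeks, plus 0.6 week for each week of gestation below 28, with SD 1.5 to 2.5 weeks;
- NEC risk about 35% higher for each week of lower gestation;
- no bundle effect, and infants undischarged at the cut excluded.

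Results over that range:

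- about 10% to 50% of September births below 28 weeks, and 0.3% to 12% of such August births, are lost;
- about 1 to 9 of 357 infants are lost in all;
- apparent NEC incidence in month 9 falls from 7% to between 4.9% and 6.5%;
- the spurious NEC rate ratio averaged over nine months is about 0.96 to 0.99.

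**Step 6: effect on the planned model.** Putting the truncated months through a Poisson model with step and trend terms (80 pre-implementation and 9 evaluation months) gives a spurious month-9 incidence rate ratio of about 0.85 to 0.95. Infants who die before the cut have a final outcome and stay in. With an assumed 50% case fatality, the month-9 ratio is about 0.96 to 0.98 if NEC survivors stay no longer than other infants, and about 0.85 to 0.92 if they stay four weeks longer. The overall range is about 0.85 to 0.98.

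**Step 7: against sampling error.** At 3 NEC cases per month, with no overdispersion or seasonal terms, the 95% interval for the month-9 ratio spans a factor of a little over 2 either way, and for the trend about ±16% per month. The artefact lies well inside both.

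**The case against.** The strongest reply is that the effect is small and the design can expose it. A handful of infants are affected, and the article itself says it can detect only about a two-thirds reduction in NEC. The control series has the same cut and the same exclusions, so an artefact would appear there too, with many more infants. The secondary logistic model tests effect modification by study group, where a common artefact would largely cancel. Monthly case-mix covariates may also be added.

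Much of this stands, and it limits the severity. It does not remove the problem. The control series is modelled separately and does not correct the East Midlands rate ratio. The covariates enter only if the periods are found to differ, and one of them, median length of stay, is itself shortened by the cut.

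A second reply is that the article does not say how infants still in hospital are classified, and the full protocol may. That is fair as to handling: their exclusion is the natural reading, not an explicit statement. But the article itself fixes the date, the claim that it suffices and the exclusion criterion, and nothing shown exempts inpatients.

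A reader might infer that the highest-risk infants are missing throughout the evaluation period, or that the cut produces a false rise in milk feeding. The document supports neither. The loss is confined to the last weeks of births. For milk at discharge, the sign depends on feeding rates by gestation, which are not given, and on whether undischarged infants are dropped or counted as not receiving milk.

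**Conclusion.** The coverage statement is not supported for infants born at about 22 to 26 weeks late in the evaluation period, and the exclusion rule as written would turn incomplete stays into selective, one-sided loss. The date arithmetic is certain; the size is not, because discharge age, gestation mix and the NEC gradient are all assumed.

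Under those assumptions the average distortion of the NEC ratio is 1% to 4%, larger at month 9, and it leaned towards the bundle in every scenario run. The illustration uses the 7% NEC figure and does not establish a size for severe NEC specifically. The concern is moderate: it is unlikely to decide the result alone, but it is an avoidable bias with a cheap remedy.

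**What to change.** Keep births to 30 September 2023 and move the end of follow-up and the database extract to a date that covers the longest stays. Early March 2024 suffices if a 22-week infant is discharged at 44 weeks PMA; a later date adds margin. State that date and correct the coverage sentence under Time period.

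Under Eligibility criteria, say how infants still in hospital at the cut are handled, and do not exclude them from the day-14 and NEC outcomes on that ground alone.

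If the date cannot move, report a sensitivity analysis omitting August and September 2023 births. Closing the birth cohort at the end of June would give up three of nine evaluation months, more than the arithmetic requires.

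The cost is a few months' delay in a routine-data extract and two amended sentences. No new participants are needed.
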